## **Data Collection Methods**

### **Face-face visits with the research nurse**

These interviews will take place at baseline (recruitment visit), 2 months, 4 months and 6 months.

The visits will include the following:

- i. check of eligibility criteria (recruitment visit only)
- ii. baseline characteristics / demographics (recruitment visit only)
- iii. collection of single saliva sample –optional (planned to be collected at the recruitment visit but can be collected at any visit according to patient preference)
- iv. examining the child's skin for disease severity and signs of infection (using the Eczema Area and Severity Index, EASI); Three Item Severity score – TIS; and Investigator Global Assessment, IGA).
- v. Patient-reported eczema severity (Patient Global Assessment, PGA) and number of skin infections treated with antibiotics or anti-viral treatments
- vi. Review of topical medication usage (prescriptions issued and changes in treatment regimen)
- vii. Review of health resource use (e.g. visits to GPs or nurses in relation to eczema treatment)
- viii. Quality of life questionnaires (at baseline and 6 months only) – dermatitis family impact questionnaire, EQ-5D, eczema utility scale and CHU-9D.

### **Treatment diaries /memory aides**

All participants will be given an eczema diary as an aide memoir to record health resource use and a sticker chart to record progress in the trial – participants randomised to wear the clothing for the first six months will have a chart where they can record when they have worn the clothing and participants randomised to the control group will have a chart to record each week they have been in the trial.

Each week the parent / legal guardian, if they have expressed a wish to complete the questions on-line will be sent a link (via e-mail) to an on-line questionnaire. This short questionnaire will be completed by referring to the diary / wall chart, and will record how their eczema has been that week, health service resource use (including, prescriptions and health professional contacts related to eczema), days of usage of: topical steroids, emollients, topical calcineurin inhibitors and wet/dry wraps, and adherence with / the clothing (intervention group only).

Participants who do not wish to complete the questions on-line will be asked to complete a form and post it back to the Clinical Trials Unit.

### **End of Trial Follow-up Questionnaire**

Parents / legal guardians of participants will be sent an end of trial follow-up questionnaire (on-line or postal) at eight months post-randomisation. This will seek information about current eczema status, adherence, acceptability and their opinion of the therapeutic clothing.

### **Concomitant Treatment**

Participants will be asked not to start new eczema treatments (other than antibiotics for infection) unless medically indicated, and will be discouraged from routinely using wet or dry wrap dressings. Any changes to a child's treatment regimen, or use of wet / dry wrapping will be recorded, but the child will remain in the trial.

### **Compliance**

Compliance with the protocol will be monitored. This will include following up patients who have not completed questionnaires and/or attended for clinic visits. Any instances of the research nurse being unblinded will be recorded. Adherence in wearing the garments will be collected weekly until 6 months and then at the end of the study (8 months). Participants randomised to wear the clothing for the first six months will have the option of using a sticker or tick chart to record the days and nights when they wear the clothing, which will act as an aid when they complete the questionnaires.

### **Criteria for terminating trial**

This trial involves CE marked clothing that are being used within their normal licensing authorisation. As such, it is very low risk. However, if severe adverse effects associated with the clothing occur frequently, the study may be terminated on the advice of the Trial Steering Committee.

The Investigator may stop the trial or terminate one centre if new information becomes available causing major safety concerns, or if there are issues with trial conduct.

Should the trial be terminated the research data will not be destroyed.

### **OPTIONAL QUALITATIVE INTERVIEW/ FOCUS GROUP**

For the sub-group who choose to participate in the qualitative study:

Data will be collected through

- 2 x child focus groups (5-8 years) n=16
- 4 x parent / guardian focus groups n=32
- Up to 10 x parent / guardian interviews, telephone or face-to-face (*only if insufficient recruitment to focus groups*)
- Up to 10 x child interview (>8 years) face-to-face (with parent / guardian present) (*only if many older children recruited to the main trial*)
- 20 x telephone interviews with prescribers and commissioners

#### Parent / guardian Focus Groups

Qualitative data will be collected from up to four audio-taped focus groups each of which will have up to eight participants; two of these groups will be run concurrently with the child focus groups. We will examine parent / guardian's experience of silk garment use and the impact this has had on the child and family.

The Investigator moderating the focus group will:

- Guide and encourage each parent / guardian to share their knowledge and experience
- Listen effectively and learn from the group
- Capture the essence of the discussion

Focus groups will be planned to ensure that they are convenient for parent / guardians; they will last for up to 2.5 hours. Each group will begin with

- Introductions
- Clarification of the purpose of the study
- Explanation of confidentiality (highlighting that whilst researchers can assure confidentiality absolute confidentiality from other members of the group cannot be guaranteed by the researcher).
- Reiteration of what is expected
- Reconfirmation that the focus group will be audio taped

- Signing of consent forms

Questions posed to the groups will be open and use straightforward conversational language, the topic guide may include

- Grand tour question
  - Tell me a bit about the eczema, what it's like living with it
- Mini tour questions
  - How have you got on with the special clothing?
  - How much did you / your child wear the clothing? (day / night / away from home)
  - What was it like wearing the clothing? (skin condition, comments from others)
  - How did you get on with looking after the garments (washing, size)
- Example questions
  - Can you tell me about any differences you have noticed? (skin condition/ behaviour / wellbeing)
- Experience questions
  - Were there particular things you or your child liked or did not like about using the special garments?
  - How would you feel about continuing to use the special clothing (what things might make you continue or make you stop, barriers to use)?
- Supplementary question
  - How did you find completing the online questionnaires and paper diaries?
  - Do you have any preferences about how this information is collected?

#### Parent / guardian interviews

In the event of inadequate recruitment to the parent / guardian focus groups we will invite parents / guardians to take part in individual, audio recorded, telephone or face-to-face interviews lasting up to 1 hour using the topic guide outlined above.

#### Child interviews

Children aged >8 will be invited to take part in individual, audio recorded face-to-face interviews lasting up to 1 hour. Depending on the age or interests of the child, they will either express their views through similar hands-on activities proposed to the younger children, or invited to have a one-on-one informal chat. They will be accompanied by a parent / guardian at all times.

Topic guide may include

- Grand tour question
  - Tell me a bit about your eczema, what it's like living with it
- Mini tour questions
  - How have you got on with the special clothing?
  - How much did you wear the clothing? (day / night / away from home)
  - What was it like wearing the clothing? (skin condition, comments from others)
- Example questions
  - Can you tell me about any differences you have noticed? (skin condition / wellbeing)
- Experience questions
  - Were there particular things you liked or did not like about using the special garments?

All digital recordings will be transcribed verbatim and then deleted from the recording device. Data including transcripts and artefacts from the child focus groups will be anonymised and stored securely on password protected computers.

#### Prescriber and commissioner interviews

Telephone interviews lasting 20-30 minutes will be planned both theoretically and technically. The interview schedule will be pre-tested and will be sent to participants prior to the interview and a convenient time for the call will be arranged. Interviews will, with permission be audio-taped and written notes recorded. In some instances participants may be both prescribers and commissioners in this case questions will be adjusted accordingly.

- What is your experience of prescribing silk garments for children with eczema?
- What makes you select this line of treatment?

- Are there any barriers to you enabling children to use these garments?
  - Perceived cost
  - Lack of evidence
  - Durability of the garments
- Do you think it is a reasonable expectation that GPs should prescribe silk garments?
- If no, who do you think is the most appropriate person to prescribe these garments?
- Do you think they should be prescribed at all? Can you explain the reason for this?

All digital recordings will be transcribed verbatim and then deleted from the recording device. Data including transcripts and artefacts from the child focus groups will be anonymised and stored securely on password protected computers.

## FILLAGGRIN GENETICS ANALYSES

Saliva testing for mutations on the gene encoding for filaggrin (FLG)

A sub-group analysis based on presence or absence of mutation(s) in the FLG will be conducted. Mutations in FLG are commonly found in eczema patients (25 -50% depending on the population(Thomas, Armstrong et al. 2002), and has been associated with disruption of skin barrier function and dry skin((Palmer, Irvine et al. 2006). As a result, there is a strong theoretical basis for thinking that children with at least one FLG mutation would be more likely to benefit from clothing, which potentially acts to improve the barrier function of the skin.

In light of this we plan to include FLG genotype as a possible predictor of treatment response in the current study.

For the sub-group analysis, study participants will be tested for up to six prevalent FLG loss-of-function mutations, depending on quality/quantity of DNA (R501X, 2282del4, R2447X, S3247X, 3702delG and 3673delC) and categorised into two groups according to FLG status:  
 Group 1: FLG ++ (no mutations) – control cohort  
 Group 2: FLG +/- (carrying one FLG null mutation) and FLG -/- (carrying two FLG null mutations)

This work will refine the phenotypic characteristics of filaggrin-deficient eczema, and will assess whether FLG genotype is an important predictive factor in determining treatment success.

### Methodology

To determine FLG genotype it will be necessary to obtain DNA from individuals entering the study. Following additional written informed consent, participants will be asked to provide a saliva sample at enrolment (or at their subsequent appointments if more practical). If children are unable to spit into the container, swabs taken from inside the cheek will be used to collect the sample.

Sample containers will be identified using the designated study number and date of birth only. Personal contact details will be kept by the Trial team and will not be transferred to the laboratory researchers.

The containers will be shipped to [name] at the Centre for Dermatology & Genetic Medicine, University of Dundee. DNA will be extracted by standard techniques and FLG genotyping for the four most prevalent null-alleles (R501X, 2282del4, R2447X and S3247X)

and depending on the quality and quantity of DNA in each individual sample, two more mutations will also be tested for (3702delG and 3673delC ). All DNA testing will be carried out according to published protocols (Sandilands, Terron-Kwiatkowski et al. 2007). Samples will be securely stored within the University of Dundee for future testing of genes associated with atopic eczema. If new techniques become available, consent will be obtained for this.

FLG genotype status will be recorded and returned to the Nottingham Clinical Trials Unit again using the study number and date of birth.

## **STATISTICS**

### **Methods**

All analyses will be carried out in accordance with CONSORT guidelines using Stata/SE 11.2 or MLwiN v2.2. Appropriate descriptive statistics will be used to compare randomised participants with those who were eligible and not randomised, and to compare the randomised arms at baseline. The primary approach to analysis will be intention-to-treat (ITT) without imputation. The primary analysis of EASI will be performed using a multilevel model (MLM) framework, with observations at 2, 4 and 6 months (level 1) nested within participants (level 2) and including baseline EASI and the stratification factors (site and age group) as covariates

Supportive analyses of the primary end point, analyses of secondary and safety end points, planned sub-group analyses, sensitivity analyses including imputation of missing outcome data and accounting for varying adherence with allocation, and any further exploratory analyses will be conducted using appropriate multivariable regression models and documented in the Statistical Analysis Plan (SAP) which will be finalised prior to unblinding of the study. Any changes in the planned statistical methods will be documented in the trial report.

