### Existing research

The 2000 HTA systematic review of eczema treatments ([Hoare, Li Wan Po et al. 2000](#)) found no RCTs looking at therapeutic clothing for the treatment of eczema, although there was some evidence to suggest that smoother fibres were less aggravating to eczematous skin ([Diepgen, Salzer et al. 1995](#)). This review has recently been updated and has revealed six small RCTs looking at therapeutic clothing for the treatment of eczema; two using silver coated textiles ([Gauger, Fischer et al. 2006](#)), ([Juenger, Ladwig et al. 2006](#)) one using MEDIELE ([Ozawa 2008](#)), one using Ethylene Vinyl Alcohol (EVOH) fibre ([Yokoyama, Kimata et al. 2009](#)) and two RCTs using DermaSilk™ ([Koller, Halmerbauer et al. 2007](#); [Stinco, Piccirillo et al. 2008](#)). These silk clothing trials were too small (22 and 30 participants respectively) and of limited duration (12 and 4 weeks respectively) to inform clinical practice.

On the basis of the limited trial data to-date, it is not possible to establish whether or not silk clothing provides measurable benefits for patients with atopic eczema. Despite the limited trial evidence, these garments are currently available on prescription in the UK and their popularity amongst patients is growing. The purpose of the optional qualitative element is to elicit detailed information from parent / guardians and children about factors that influence the use of silk clothing and to understand prescribers / commissioners view on the use of silk garments. Qualitative data will be aligned with quantitative findings to provide a rounded understanding of garment usage including barriers and enablers.

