**Table 1 - Pilot stop/go criteria**

| Criteria to be assessed at 6 months of recruitment | Proposed action                                                                             |
|----------------------------------------------------|---------------------------------------------------------------------------------------------|
| ≥90% of target recruitment & retention             | Continue with main trial as planned                                                         |
| 70% to 89% of target recruitment & retention       | Continue with main trial. Implement strategies for improvement.                             |
| 50% - 69% of target recruitment & retention        | Urgent measures required, discuss plans with Trial Steering Committee and NIHR HTA          |
| <50% of target recruitment & retention             | Stop trial unless good reason for delay and rectifiable solution can be readily implemented |

Adherence in wearing the clothing will be assessed regularly by the TMG in the intervention group only, and will act as a trigger for concern if participants report using the clothing less than 50% of the time.

The Sponsor reserves the right to discontinue this study at any time for failure to meet expected enrolment goals, for safety or any other administrative reasons. The Sponsor shall take advice from the Trial Steering Committee as appropriate in making this decision.

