#### **Standard care:**

All participants (active and control groups) will continue with their standard eczema care in line with NICE guidance ([NICE December 2007](#)). No efforts will be made to intervene or change a child's standard eczema care unless the research nurse thinks that the skin may be infected. If research nurses suspect infection they will recommend that the patients contact their normal medical team (GP, Nurse, dermatologist) as appropriate.

Standard advice about what clothing to use for a child with eczema will be provided (avoid wool, and wear cool loose clothing – especially cotton and linen), but specific products will not be recommended.

If a child is currently using "specialist" cotton clothing (e.g. special sleep suits with built-in mittens), the use of these garments will be recorded, but will not be grounds for exclusion. However, participants in the control group will be asked to refrain from using prescription clothing (including silk clothing and synthetic garments used for wet wrapping) during the trial.

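### Weekly clothing use is recorded in the intervention arm only, so the planned adherence analysis cannot measure silk use by controls in months 0 to 6

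*Protocol*

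**What the plan says.** The primary analysis does not use adherence: "The primary approach to analysis will be intention-to-treat (ITT) without imputation" (Statistics, Methods). The same section plans sensitivity analyses "accounting for varying adherence with allocation, and any further exploratory analyses will be conducted using appropriate multivariable regression models", to be "documented in the Statistical Analysis Plan (SAP) which will be finalised prior to unblinding of the study".

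Allocation has two sides. Under Standard care the Protocol defines the control side (wording: "participants in the control group will be asked to refrain from using prescription clothing (including silk clothing and synthetic garments used for wet wrapping").

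Recording covers one side. The weekly items listed under Treatment diaries /memory aides end with clothing use for one arm (wording: "adherence with / the clothing (intervention group only"). In the same section, "participants randomised to the control group will have a chart to record each week they have been in the trial". The text below Table 1 says: "Adherence in wearing the clothing will be assessed regularly by the TMG in the intervention group only".

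The route to control use is also described. Existing research notes that "these garments are currently available on prescription in the UK and their popularity amongst patients is growing". Participants are not blinded (Randomisation and blinding). The exclusion criteria bar current silk users only if they are unwilling to stop, so some controls may already own garments.

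**The concern.** The Protocol gives controls an instruction and plans an analysis that depends on whether it was followed, but states no item that measures it during the randomised period. If the trial finds little or no difference, readers will ask whether the garments do not work, were not worn, or were also worn by controls. The weekly data can address the second explanation. They cannot directly address the third.

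This is a data-collection gap, so a later SAP cannot close it: weekly use that was never asked about cannot be recovered reliably at the end. The Protocol itself says under Sample size and justification that a repeat of such a trial is unlikely.

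**Working it through.** **1. What is asked of whom, months 0 to 6**

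| Source in the Protocol | Intervention | Control |
|---|---|---|
| Weekly questionnaire, clothing item | Asked | Not asked |
| Wall chart | Clothing worn | Weeks in trial |
| TMG adherence review | Yes | No |
| Nurse visits | Clothing must not be mentioned | Clothing must not be mentioned |
| Weekly wrap use and eczema-related prescriptions | Yes | Yes |
| Regimen changes; NHS and family resource use | Yes | Yes |

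The Adherence row of Table 2 names no arm, but it refers to the weekly questionnaire, whose clothing item is limited to the intervention group. The 8-month question on clothing use comes two months after controls receive garments, so it does not describe months 0 to 6.

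**2. Figures in the plan**

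The Protocol gives no expected wear rate and no expected control use. Its only adherence figure is the 50% trigger for concern below Table 1. The rates used here are assumptions: wear in the intervention arm pT = 70% (range 50% to 90%), control use pC = 0 to 20%.

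The sample size statement supplies the scale: 3 EASI points, SD 13, correlation 0.6, 10% loss. For one baseline and three follow-up measures:

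- variance factor = (1 + 2 × 0.6)/3 − 0.6² = 0.7333 − 0.36 = 0.3733
- effective SD = 13 × √0.3733 = 7.94
- n per arm = 2 × (1.960 + 1.282)² × 7.94²/3² ≈ 148, or 296 in total, which matches 300 before loss is applied
- with 270 analysed (135 per arm), power for 3 points is about 87%

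This serves only as the base for step 4. The present point does not depend on it.

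**3. Effect of wearing, estimated with and without control data**

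Take a true effect of wearing of 3 points. Then:

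- ITT effect = 3 × (pT − pC)
- estimate that takes control use as zero = ITT/pT
- estimate using both arms = ITT/(pT − pC)

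With pT = 70%:

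| pC | ITT effect | Control use taken as zero | Shortfall | Both arms recorded |
|---|---|---|---|---|
| 0% | 2.10 | 3.00 | 0% | 3.00 |
| 5% | 1.95 | 2.79 | 7% | 3.00 |
| 10% | 1.80 | 2.57 | 14% | 3.00 |
| 20% | 1.50 | 2.14 | 29% | 3.00 |

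Across the range of pT, with pC between 5% and 20%, the shortfall runs from 6% (pT = 90%, pC = 5%: 2.83) to 40% (pT = 50%, pC = 20%: 1.80).

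A simulation with 270 analysed, 2,000 runs and a true effect of −3 agrees. With adherence unrelated to prognosis, the estimate from intervention-arm data alone was −2.97, −2.80, −2.61 and −2.12 at pC = 0, 5, 10 and 20%. With both arms recorded it stayed between −2.97 and −3.05.

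**4. Dilution of the ITT effect**

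To isolate control use, assume full wear in the intervention arm, so that ITT = 3 × (1 − pC). At 135 per arm, power falls from about 87% with no control use to 84% (2.85 points), 80% (2.70 points) and 70% (2.40 points) at 5%, 10% and 20%. Without a control-arm item, nobody can tell which of these applies.

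**The case against.** The strongest reply has four parts.

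- **The method belongs to the SAP.** A reader might infer that multivariable regression here means comparing adherent families with the rest, which would lose the protection of randomisation. The Protocol does not say so. Its phrase covers many analyses, does not make adherence a covariate and does not exclude non-adherers. A complier-average estimate with randomised arm as the instrument can itself be fitted as a regression. This part stands in full: there is no finding against the estimator.
- **Intervention-arm data may be enough.** A reader might also infer that the adherence analysis cannot be valid. That goes too far. If control use is nil, the intervention-arm data give an unbiased complier effect. If it is not nil, the bias is towards zero and can be bounded. This stands, but the bound needs a figure for control use, and the trial will not have a direct one.
- **Control use is not wholly unseen.** Prescriptions and resource use are collected in both arms, Concomitant Treatment records regimen changes, and family costs could show purchases. This stands in part. None of these is a silk item, garments already owned could be missed, and a prescription does not show wearing.
- **The effect is small against the noise.** The standard error of the complier estimate at 70% wear is about 7.94 × √(2/135)/0.70 = 1.38 points. The bias is 0.21 points at 5% control use and 0.86 at 20%. At 5% it is indeed lost in the noise; at 20% it is about 0.6 of a standard error. Crossover is also discouraged by excluding users unwilling to stop and by giving controls garments at six months.

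**Conclusion.** The point holds as a gap in data collection. Silk use by controls in months 0 to 6 is not directly recorded. The planned sensitivity analysis for adherence with allocation therefore cannot measure non-adherence in the control arm, and dilution of the ITT effect cannot be assessed.

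On assumed rates, with 70% wear, a complier estimate that takes control use as zero is unbiased at 0% control use and 7%, 14% and 29% too small at 5%, 10% and 20%. These figures treat wearing as yes or no, give wearing the same effect in both arms, and let allocation act only through wearing. The Protocol supplies none of the rates, and true control use could be nil.

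The primary ITT comparison remains valid as a comparison of allocated groups. The documents do not support the stronger conclusions that the adherence analysis is bound to be invalid or that a biased regression has been planned. This is a cheap improvement to a sensitivity analysis and to the reading of a null result, not a fault in the primary analysis.

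**What to change.** Under Treatment diaries /memory aides, remove the restriction to the intervention group and ask both arms the same weekly item: whether any silk or other prescribed clothing was worn that week, and how often. State in the Adherence row of Table 2 that it applies to both arms. Responses go to the trials unit on-line or by post, as now, and not to the research nurse, so nurse blinding is unaffected. State in Methods that the adherence sensitivity analysis will use the data from both arms, and leave the estimator to the SAP.

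The cost is one extra question on a form that controls already complete. Two limits should be accepted openly: the question may remind controls of silk, and controls who were asked to refrain may under-report use. Even so, a reported rate is a better basis than an assumed zero.
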